### RNA extraction and transcriptomics analysis

Total RNA will be extracted from all samples using a commercially available kit (Qiagen). The quantity and quality of the extracted RNA will be measured by Agilent bioanalyser. Sequencing libraries will be generated from 1 μg of RNA using the Truseq RNA library preparation kit (Illumina) before being converted to complimentary DNA (cDNA). cDNA libraries will then be sequenced (Illumina HiSeq). Raw read quality filtering and adapter trimming will be performed with Trimmomatic before building of the transcriptome index with Spliced Transcripts Alignment to a Reference (STAR) Software [29]. Collation of individual sample counts into a m x n matrix for differential abundance testing will be performed utilising R using t-tests after total-count normalisation. The false discovery rate (FDR) will be determined to control for multiple comparison testing. Furthermore, Gene Set Enrichment Analysis (Broad Institute) will be used to determine pathway-specific alterations in gene expression, which will give new insights into the pathogenesis of AC. Differentially expressed genes will undergo further bioinformatics analysis to identify genes that contain an export sequence motif common to all secreted proteins [30]. In addition, differentially expressed genes encoding proteins that are exported via exosome vesicles will also be identified [31]. Identified candidate genes will be confirmed by quantitative PCR. PCR data will be expressed as mean ± SEM, and differences between groups will be assessed using t-tests and considered statistically significant when *p* < 0.05. Potential biomarker genes that are significantly different between groups will guide analysis of plasma and urine samples from AC and control patients to generate information relating to specific biomarkers.

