The major pathological features of AC are inflamed glenohumeral and subacromial synovium, and thickening and contracture of joint capsule, particularly the rotator interval and coracohumeral ligament [1]. Inflammatory and fibrogenic cells and mediators such cytokines, macrophages and mast cells are elevated in AC capsular tissues compared to controls [15–17]. Inflammatory processes might initiate fibroblast proliferation and fibrotic processes, producing an imbalance between extracellular matrix tissue degradation, remodelling and regeneration; this disequilibrium might lead to fibrosis [1, 18]. Fibroblasts might also transform into myofibroblasts and cause capsular contracture [19], but myofibroblasts, also found in Dupuytrens disease associated with AC [20], have not been found in all AC tissue samples [21]. Neoangiogenesis and neoinnervation also occur in AC; the latter process may explain why AC can be intensely painful [1].

Although the macroscopic and histological features of AC are well described, the underlying pathogenic processes are less understood [18, 22]. In primary idiopathic AC, the aetiology is uncertain [22]. In secondary AC, there may be a history of trauma or surgery, myocardial infarction, type I or type II diabetes mellitus, hypothyroidism, or Parkinson disease [22]. Arkikila et al. [23] found the incidence of AC in people with type I or type II diabetes was 10 and 22% respectively.

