The transcriptional profile of AC has received little research attention [12]. Evidence suggest a genetic predisposition towards AC using family history and racial predilection as markers for genetic association [22]. Identification and functional analysis of changes in gene expression associated with AC might help understand its pathogenesis [24]. Cui et al. [24] used RNA-sequencing to investigate the pathogenesis of idiopathic AC by comparing five tissue samples from people with AC to two people with acromioclavicular dislocation patients. One-hundred and eighty-eight differentially expressed genes were identified which encode proteins such as matrix metalloproteinases and cytokines. Hagiwara et al. [21] compared tissue samples from 12 people with idiopathic AC shoulders to18 people with rotator cuff tears and found the expression of 44 genes were significantly different; these genes related to fibrosis, inflammation, chondrogenesis and angiogenesis. Increasing the statistical power for these analyses might reveal new insights in AC pathogenesis and identify new biomarkers for diagnosis and treatment.

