### Study aims

The primary aim of the current study is to investigate gene expression alterations in people with primary and secondary AC compared to people with non-inflammatory shoulder instability (controls). Secondary aims are: 1) to interrogate gene expression data to identify potential serum and urine biomarkers that might assist in the early diagnosis and staging of AC; and 2) investigate clinical outcomes in people with AC compared to controls 12-months following arthroscopic capsular release or labral repair respectively.

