### Sample size

The majority of the molecular parameters being compared in this study are new in this disease setting and few datasets exist from which to estimate the sample size. Hagiwara et al. [21] found significant differences in gene expression for 33 genes with 12 AC and 18 control samples. To increase the likelihood of detecting differences in gene expression between our groups, we plan to recruit 25 participants per group. This sample size represents a pragmatic decision, based on our expectation of being able to recruit 50 participants over a two-year period, and our desire to increase the statistical power of our study compared to other research.

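### Total-count normalisation in the primary RNA-seq comparison can make unchanged genes look down-regulated in adhesive capsulitis, and FDR adjustment cannot correct it

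*Protocol article*

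**What the plan says.** The section on RNA extraction and transcriptomics analysis in the Protocol article fixes the method: "differential abundance testing will be performed utilising R using t-tests after total-count normalisation". Multiplicity is handled afterwards: "The false discovery rate (FDR) will be determined to control for multiple comparison testing". No threshold is named there. Gene Set Enrichment Analysis follows. The differentially expressed genes are then filtered for secreted and exosome-exported proteins, selected candidates go to quantitative PCR, and the survivors guide the plasma and urine work.

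This comparison serves the main objective (Study aims): "The primary aim of the current study is to investigate gene expression alterations in people with primary and secondary AC". On size, the Sample size section says "we plan to recruit 25 participants per group" and calls this a pragmatic choice.

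The Background describes the AC tissue as showing "inflamed glenohumeral and subacromial synovium, and thickening and contracture of joint capsule". It offers a mechanism in hedged terms: "Inflammatory processes might initiate fibroblast proliferation and fibrotic processes, producing an imbalance between extracellular matrix tissue degradation, remodelling and regeneration". Of an earlier study's differentially expressed genes it says that "these genes related to fibrosis, inflammation, chondrogenesis and angiogenesis".

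**The concern.** Each library is prepared from a fixed 1 μg of RNA, and the counts are then scaled to a common total. The scaled values are therefore shares of a whole. If some highly expressed transcripts take a larger share in one group, all the others must take a smaller one, even when their own expression has not changed. A fibrotic capsule that produces more of a few abundant matrix transcripts would do exactly this, and the Background makes such a shift plausible.

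The resulting error is a common downward shift in AC across the unchanged genes. FDR procedures take the null p-values as valid and correct only for their number. A larger sample does not help either, because the standard error shrinks while the shift stays. At stake are the list of differentially expressed genes, the direction of pathway findings, and the choice of candidates for the biomarker stage.

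**Working it through.** The documents give no power, effect size or expected error rate for this comparison, so there is no figure to reproduce.

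**Inputs from the Protocol article.** Total-count normalisation, a t-test per gene, FDR for multiplicity, 25 per group.

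**Assumed inputs.** The share s, the fold rise f, the dispersion, the number of genes and of truly changed genes, and Benjamini-Hochberg at 5%.

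**Step 1: size of the shift.** Set the total in controls to 1. In AC the raised transcripts contribute s·f and the rest 1 − s, so the total is 1 − s + s·f. After scaling, an unchanged gene is multiplied by 1/(1 − s + s·f):

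- s = 5%, f = 2: 1/1.05 = 0.952
- s = 10%, f = 2: 1/1.10 = 0.909
- s = 20%, f = 2: 1/1.20 = 0.833
- s = 20%, f = 3: 1/1.40 = 0.714

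**Step 2: effect on one unchanged gene.** Take a natural-log SD of 0.5 (assumed). The standard error with 25 per group is 0.5 × √(2/25) = 0.141. The chance of a two-sided p < 0.05 in the downward direction is about Φ(ln(1 − s + s·f)/0.141 − 1.96), against a nominal 2.5%. For the four settings above this gives 5%, 10%, 25% and 66%.

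**Step 3: effect on the gene list.** Two negative-binomial models were simulated, each with 12,000 genes and 25 v 25.

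- Model A: 20 abundant genes raised f-fold, 500 others changed 2-fold up or down, dispersion 0.25, 5 repeats, t-tests on log and on raw normalised counts.
- Model B, with close variants: 40 abundant genes raised, 3% of genes changed by ±0.8 log2, dispersion 0.2 or 0.5, 4 repeats.

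Realised false discovery proportion with total-count scaling (nominal 5%):

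| s, f | Dispersion 0.2 to 0.25 | Dispersion 0.5 |
|---|---|---|
| 5%, 2 | 4% to 8% | 4% |
| 10%, 2 | 18% to 27% | about 5% |
| 20%, 2 | 52% to 79% | 25% to 27% |

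In model A with log counts and no shift, the proportion was 5.7%. At s = 10%, f = 2 there were about 92 false calls, 91 of them downward. At s = 20%, f = 2 there were about 433, nearly all downward. A 3-fold rise gave 57% at s = 10% and 92% at s = 20%. Raw counts gave nearly the same proportions as log counts.

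**Step 4: change only the scaling.** On the same data, median-of-ratios size factors kept the proportion at about 6% or less in every setting. In model A with the same t-test it was 3.1% to 5.5%, with false calls split roughly evenly up and down. Power for truly changed genes at s = 20%, f = 2 (log counts) was 88%, against 77% with total-count scaling.

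**The case against.** **The condition is not documented.** The harm needs transcripts that hold a large share of reads and rise together in AC. The Background describes gross tissue changes and lists gene categories. It gives no read share, fold change or direction, it words the fibrotic mechanism as a possibility, and it notes that myofibroblasts were not found in all samples. This stands. A reader might infer that FDR control is bound to fail and that most of the list will be false. The documents do not support that: at s = 5%, f = 2 the error is close to nominal.

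**The result depends on dispersion.** The AC group mixes primary and secondary disease, and participants range from 18 to 70 years with no upper limit on symptom duration, so high dispersion is plausible. At dispersion 0.5 far fewer genes are called. At s = 20%, f = 2 about 22 of 81 calls were false (27%). This also stands, though the bias is reduced and not removed.

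**The t-test is not at fault.** A reader might infer that a plain t-test on RNA-seq data is itself invalid here. The check does not support that: with 25 per group it held FDR once the scaling was changed.

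**qPCR is a safeguard.** It may catch false candidates if its reference genes are stable. It covers only selected candidates, however, and does not repair the full list or the enrichment result.

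**The comparison favours the alternative.** Median-of-ratios and TMM assume that most genes are unchanged, and the simulations set about 96% to 97% of them so. If inflammation alters the cell mix broadly, that assumption is strained too. This is a reason to check it, not to keep total counts.

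**A journal article condenses.** That excuses omissions, but the normalisation is stated, not omitted.

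**Conclusion.** The point holds as a conditional risk to the primary analysis. The stated normalisation can push unchanged genes down in AC, in the kind of tissue the study expects to find, and the FDR step cannot detect or correct this. With 25 per group the consequence runs from negligible to a gene list that is mostly false, depending on s, f and dispersion. All three are unknown from the documents, and the stated method has no step that would show which case applies. The mechanism and its direction are arithmetic; the percentages rest on the assumed settings. The scaling is the cause, not the test. This should be fixed before the data are analysed, but the documents do not show that the planned analysis is certain to fail.

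**What to change.** Replace total-count normalisation with TMM or median-of-ratios size factors. Use the same normalised data for gene-set enrichment, and apply Benjamini-Hochberg at a stated threshold such as 5%. Possible wording: counts will be scaled with TMM (or median-of-ratios) size factors; groups will be compared gene by gene with Benjamini-Hochberg control of the FDR at 5%; enrichment analysis will use the same scaled data.

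A moderated or count-based model (limma-voom, edgeR, DESeq2) is a convenient way to do this but is optional.

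Because these size factors assume that most genes are unchanged, add a check. Compare size factors with library totals by group and report any systematic difference. A group difference would signal a composition shift, and a very broad one would call for caution with either scaling.

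The cost is a change of wording and free R software. No new samples, sequencing or participants are needed.

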## Background

Adhesive capsulitis (AC), or ‘frozen shoulder’ is a debilitating pathological condition of the glenohumeral joint, characterised by stiffness, pain and dysfunction [1, 2]. The condition is estimated to affect 2–5% of the general population, most commonly in women and people aged 40 to 60 years [3, 4]. The natural history of AC has been described as self-limiting, with resolution of symptoms within 2 years [5]. However, many people experience prolonged symptoms and functional limitations [6]. Hand et al. [7] found that 41% of 223 patients reported ongoing symptoms at 4 years following symptoms onset, with 6% still reporting severe pain and functional loss.

Diagnosing AC is usually based on clinical findings [6]. The American Shoulder and Elbow Surgeons consensus definition describes AC as “functional restriction of both active and passive shoulder motion for which radiographs of the glenohumeral joint are essentially unremarkable except for the possible presence of osteopenia or calcific tendonitis” [8]. However, in the absence of objective criteria, particularly in the early-stage AC [9], diagnosis can be contentious [10]. Patients usually report the onset of shoulder pain before loss of motion [11, 12]. External rotation is often the first reported movement restriction [1, 13], which is thought to be consequential to contraction of the coracohumeral ligament, one of the essential diagnostic findings in AC [1]. X-rays can be used to rule out other causes of shoulder pain and stiffness [14]. Ultrasound, magnetic resonance imaging (MRI) and magnetic resonance arthrography can detect features suggestive of AC such as capsular thickening, and loss of the inferior axillary pouch and joint volume [14]. Blood tests are usually normal, though cholesterol, triglycerides and C-reactive protein might be elevated in the early stages [10].

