### Eligibility criteria

Eligible participants have the following characteristics:18 to 70 years of ageSymptoms > 3 monthsNormal x-rayNo evidence of arthropathy or full thickness rotator cuff tear on bloods and MRIMRI studies will be performed on minimum 1.5 T scanners using the sequences: axial T1-weighted, coronal oblique T2-weighted with and without fat saturation, axial and sagittal oblique proton density, and sagittal oblique T2 fat saturationAC group (diagnosis based on consensus definition [8])Primary or secondary ACLoss of shoulder active motion > 30% in all directions compared to unaffected side including at least 50% reduction in external rotationComparison groupGreater than one episode of glenohumeral instability, defined as documented dislocation with labral tear on MRINo episode of instability in eight weeks prior to surgery (to reduce the likelihood of acute post-traumatic inflammatory reaction in the shoulder capsule)Willing, able and mentally competent to provide informed consent (able to read and understand the Patient Information and Consent Form which is written in English language).

People who have the following characteristics are not eligible:Bilateral shoulder pain or reduced motion affecting daily livingPrior shoulder surgery

Consecutive patients who fulfill the eligibility criteria will be invited to participate by a study surgeon at the pre-operative assessment. Informed written consent will be obtained as appropriate. Participation in the study is voluntary; no financial incentives will be offered, and recruitment will occur over a 2-year period, commencing in 2016.

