### Clinical outcomes

Patient reported outcome measures will be collected pre-operatively and 12-months post-operatively and include the Oxford Shoulder Score [32], Oxford Shoulder Instability Score [33], Disabilities of the Arm, Shoulder, and Hand Questionnaire Short Version (Quick DASH) [34], American Shoulder and Elbow Society Score [35], and the EQ-5D-5 L [36]. Standardised data collection will be overseen by the study’s research manager. Active range of movement of the affected shoulder will be assessed by the patient’s surgeon pre-operatively and 12-months postoperatively. To maximise follow up rates, assessment of 12-month outcomes will be aligned with the study centre’s registry research program which routinely collects 12-month postoperative data [37].

Outcome data will be summarised using means with standard deviations or medians with lower and upper quartiles if the data are skewed. Outcomes for AC and control participants will be compared pre-operatively and at 12 months using linear regression, adjusted for potential confounders such as age, employment status and dominant arm. Tests will be considered significant when *p* < 0.05. The limitations of comparing inherently different groups, for example with different pathology and treatment, will be recognised when interpreting the results.

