### Demographic data

At the pre-operative assessment, the following information will be collected from each participant: age, sex, employment status, dominant arm, symptom duration, employment status, type of work (e.g. heavy manual), prior treatment (e.g., physiotherapy, corticosteroid injection, hydrodilation), comorbidities and current medications.

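### The primary gene-expression t-tests and their qPCR confirmation adjust for neither age nor sex, so age- or sex-related genes may be reported as AC genes

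*Protocol article*

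**What the plan says.** The Study aims section puts the molecular comparison first: "The primary aim of the current study is to investigate gene expression alterations in people with primary and secondary AC compared to people with non-inflammatory" (the sentence goes on to name the instability controls).

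The section on RNA extraction and transcriptomics analysis names the test. Differential abundance is assessed "using t-tests after total-count normalisation". On multiplicity it says: "The false discovery rate (FDR) will be determined to control for multiple comparison testing". For the qPCR confirmation of candidate genes, "differences between groups will be assessed using t-tests and considered statistically significant when" p < 0.05. No covariate is named at either step, and no separate sample is named for qPCR.

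Four other places bear on this:

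- Background: AC occurs "most commonly in women and people aged 40 to 60 years".
- Eligibility criteria: one age range, 18 to 70, serves both groups. Recruitment is described thus: "Consecutive patients who fulfill the eligibility criteria will be invited to participate by a study surgeon at the pre-operative assessment". No matching or stratification on age or sex is described.
- Clinical outcomes: the same two groups are compared by linear regression, "adjusted for potential confounders such as age, employment status and dominant arm".
- Demographic data: the baseline items include "age, sex, employment status, dominant arm, symptom duration".

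**The concern.** A two-sample t-test has no place for a covariate. If the groups differ in age or sex, a gene whose expression follows age or sex will differ between the groups without any link to AC. The protocol gives reason to expect such a difference on the AC side, does nothing in the design to prevent it, and treats age as a confounder between these groups, but only for a secondary aim. It gives no reason for handling the primary aim differently.

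At stake is what the gene list means. FDR control limits chance findings; a confounded gene is not a chance finding, because its group means really do differ. The qPCR step repeats the same unadjusted contrast, so it would tend to confirm such a gene. The surviving genes then guide the plasma and urine biomarker work.

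**Working it through.** **Inputs from the protocol.** 25 participants per group (Sample size); per-gene t-test with FDR control, threshold not stated; qPCR t-test at p < 0.05. The sample size is described as pragmatic, with no alpha, power or effect size, so there is no stated figure to reproduce. The protocol gives no age or sex distribution for either study group. Every imbalance below is an assumption, shown as a range.

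**Step 1: one gene at a time.**

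- Gene expressed only in men, with proportions of women pA and pB: t = (pA − pB) / √{[pA(1 − pA) + pB(1 − pB)] / 24}.
  - 60% vs 20% women: 0.4 / √(0.40/24) = 3.1, p = 0.003.
  - 70% vs 10% women: 0.6 / √(0.30/24) = 5.4, p = 2 × 10⁻⁶.
- Gene correlated 0.4 with age within groups: spurious difference = 0.4 × (age gap / SD), and t = difference / √(2/25).
  - 20-year gap, SD 10: 0.4 × 2 = 0.8 SD, t = 0.8/0.283 = 2.8, p = 0.007.
  - 24-year gap, SD 8: 0.4 × 3 = 1.2 SD, t = 1.2/0.283 = 4.2, p = 10⁻⁴.

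**Step 2: do these survive FDR control?** Assume Benjamini-Hochberg at 5% over 15,000 genes. A p-value is called only if at least p × 15,000 / 0.05 genes have p-values that small.

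- p = 0.003 needs 900 genes.
- p = 0.007 needs 2,100 genes.
- p = 10⁻⁴ needs 30 genes.
- p = 2 × 10⁻⁶ needs 0.6, so it is called on its own.

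The weaker cases in Step 1 need not reach the list; the stronger ones plausibly would. Nominal p-values alone do not settle the size.

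**Step 3: whole-list simulation.** 25 vs 25, 15,000 genes, 40 runs per scenario, Benjamini-Hochberg at 5%. Assumed: 1,000 genes that depend on age only (0.3 SD per 10 years), 50 on sex only (3 SD), and 1,000 true AC genes (1 SD). Ages were limited to 18–70. The counts and realised FDR are means for the unadjusted t-test; the two p < 0.05 columns also cover runs without true AC genes.

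| Imbalance | Women, AC vs control | Mean age (SD), AC vs control | Age-only genes p < 0.05 | Sex-only genes p < 0.05 | Age-only genes called (of 1,000) | Sex-only genes called (of 50) | Realised FDR |
|---|---|---|---|---|---|---|---|
| None | 50% vs 50% | 50 (8) vs 50 (8) | 5% | 4–5% | 2 | 0 | 5% |
| Mild | 60% vs 45% | 50 (8) vs 44 (10) | 8–10% | 10–11% | 5 | 1 | 5% |
| Moderate | 60% vs 30% | 50 (8) vs 36 (10) | 27–29% | 40–48% | 45 | 4 | 11% |
| Strong | 65% vs 15% | 52 (8) vs 27 (8) | 71–72% | 87–89% | 338 | 28 | 37% |

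With no true AC genes at all, fewer than one gene per run was called under mild or moderate imbalance. Under strong imbalance about 152 age genes and 18 sex genes were called.

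The p < 0.05 columns also bear on qPCR, which is judged at that level: under moderate imbalance an unadjusted t-test would pass over a quarter of such age genes even without selection by RNA-seq.

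**Step 4: the same data with group + age + sex in the model.** The share of age-only and sex-only genes with p < 0.05 returns to about 5% in every scenario.

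| Imbalance | Realised FDR, adjusted | Variance factor of group effect | True AC genes called (of 1,000), unadjusted → adjusted |
|---|---|---|---|
| Mild | 5% | about 1.2 | 618 → 496 |
| Moderate | 4% | about 1.8 | 629 → 191 |
| Strong | 3% | about 4.6 | 684 → 5 |

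**The case against.** **The imbalance is not documented.** A reader might infer that the groups will differ in age and sex and that such genes will be reported as AC genes. The protocol does not support that certainty. The Background describes AC in the general population, not this surgical cohort. Nothing describes the age or sex of the instability patients, and the 18–70 range applies to both groups. The examples of confounders for the clinical outcomes name age but not sex. This stands: the supportable word is "may", and under mild imbalance the harm is negligible.

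**FDR control and later filters reduce the harm.** In part. Step 2 shows that modest confounding often fails the FDR cut-off. Biomarker candidates must also carry a secretion motif or be exported in exosomes, and nothing shows that age or sex genes would pass that filter. But neither device separates AC from age or sex, and qPCR repeats the same contrast.

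**An article condenses its protocol.** Covariates could be left to a fuller document. Here, though, a specific test is named for both steps, and it cannot take covariates.

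**Adjustment costs power in an exploratory study.** True, and substantial (Step 4). It does not rescue the t-test: under strong imbalance more than a third of its calls are false.

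Two further inferences should not be drawn. Pooling primary and secondary AC is not an error, because the primary aim names both; adjusting for HbA1c could remove part of what that aim sets out to study. Nor is there a case for excluding sex-chromosome genes, which is largely redundant once sex is in the model.

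**Conclusion.** The point holds as a risk built into a stated method. The primary RNA-seq comparison and its qPCR confirmation are unadjusted, the design does not balance age or sex, and the protocol itself adjusts for age when it compares these groups on clinical outcomes. Genes related to age or sex may therefore be reported as AC genes.

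The size cannot be fixed from the protocol. It ranges from negligible under mild imbalance to serious under strong imbalance, where realised FDR is about 37% against a nominal 5%. These results rest on the assumed age and sex mixes, the assumed gene effects and number of genes, and a 5% Benjamini-Hochberg threshold that the protocol does not state. The adjusted results also assume that age acts linearly, as it was simulated.

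**What to change.** - Replace the t-tests with a per-gene linear or count model containing group, age and sex, for both RNA-seq and qPCR.
- Select biomarker candidates from the adjusted list. Keep the unadjusted list as a sensitivity analysis.
- Report the age and sex distribution of each group and how far the ages overlap.
- State that AC and age cannot be separated where the ages do not overlap.

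No new data are needed, since age and sex are already collected. The cost is precision. With the variance factors above, the standard error of the group effect grows by about √1.2 = 1.10, √1.8 = 1.34 and √4.6 = 2.14, so fewer genes are called, and very few if the groups hardly overlap. In that last case adjustment alone cannot rescue the comparison. Only matched or age-restricted controls could, and the overlap report is what would tell the reader so.
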